### Statistical analysis

An independent statistician blinded to group allocation will perform statistical analysis using SAS® Version 9.4 (SAS institute. Inc., Cary, NC). All statistical analyses will be two-tailed, and the significance level will be set at 5%.

Three types of analysis sets will be used in this study, as follows: intention to treat (ITT) analysis set, full analysis set (FAS), and per-protocol (PP) set. The ITT analysis set will be comprised of the data from every participant who had been randomly assigned to any group in this trial. The FAS set will include the data from all participants who ever received the intervention and provided assessment data at least once following random allocation. The PP set will include only the data from participants who completed the trial without any major violation of the protocol. The FAS will be the primary set for the efficacy analysis, and sensitivity analysis will be conducted to compare the results from the FAS and PP sets. For safety analysis, the ITT set will be the primary set, and the PP set will be used as a supplement. The multiple imputation method will be adopted to handle missing data in incomplete data sets.

Summary statistics of demographic characteristics and baseline measurements of the variables of each group will be presented. Continuous data will be expressed as the mean ± standard deviation, but median and 95% confidence intervals will be provided if necessary. Between-group differences will be analyzed using analysis of variance (ANOVA) or the Kruskal-Wallis test. Categorical data will be presented as frequencies with percentiles and analyzed using the Chi-square test or the Fisher’s exact test.

The primary outcome measure of this study will be the mean change of average BFI scores acquired at baseline and week 9. To validate significant changes in BFI between groups, we assumed two sets of hypotheses.

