### Intervention

There are three arms in this trial. All participants regardless of their assignment will be educated via a brochure on how to manage daily life to alleviate the cancer-related fatigue.

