#### Usual care group

The participants in the usual care group will not receive moxibustion treatment. They will maintain their usual treatment and self-care but will not begin any additional treatment to improve their cancer-related fatigue during the study.

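### The primary efficacy set depends on treatment received, which filters moxibustion and usual care unequally in the gatekeeping comparison, and no efficacy role is stated for the all-randomised set

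*Protocol article*

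**What the plan says.** The Statistical analysis section of the protocol article defines three sets.

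- **ITT:** the data of "every participant who had been randomly assigned to any group in this trial".
- **FAS:** the data of "all participants who ever received the intervention and provided assessment data at least once following random allocation".
- **PP:** participants who finished the trial with no major protocol violation.

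On their use it says "The FAS will be the primary set for the efficacy analysis", with a sensitivity analysis that sets the FAS against the PP set. The ITT set appears once more: "For safety analysis, the ITT set will be the primary set, and the PP set will be used as a supplement". On missing data it says "The multiple imputation method will be adopted to handle missing data in incomplete data sets".

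The Usual care group section says "The participants in the usual care group will not receive moxibustion treatment". The opening of the Intervention section says "All participants regardless of their assignment will be educated via a brochure on how to manage daily life to alleviate the cancer-related fatigue".

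The same Statistical analysis section tests H01 (moxibustion versus usual care) first, and tests H02 (moxibustion versus sham) only if H01 is rejected.

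**The concern.** Entry to the primary efficacy set depends on two things that can be settled after allocation: having received the intervention and having given an assessment. The first has an obvious meaning where there are sessions to attend. It has no stated meaning in usual care, where there are none. A participant who is allocated to moxibustion and never comes for a session leaves the primary analysis. A participant who is allocated to usual care and is equally disengaged has no comparable event to fail.

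This matters most for H01. The Blinding section says that usual care participants will know their group, and the primary outcome is a self-completed fatigue score. Failing to start can therefore follow from knowing the assignment and can be related to the outcome. H01 is also the gate to H02, so a distortion in H01 decides whether the sham comparison is tested at all.

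The planned safeguards do not reach the problem. The PP set requires completion, so comparing it with the FAS cannot show what happens when never-starters are put back. Multiple imputation within the FAS cannot restore people who were never in the FAS.

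**Working it through.** **1. The plan's own figures.** The inputs from the Sample size calculation section are a difference of 1.6, SD 2.0, 5% significance, 80% power and 20% drop-out. The test is two-sided (Statistical analysis).

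- n per group = 2 × (1.960 + 0.842)² × 2.0² / 1.6² = 24.5, rounded up to 25.
- With drop-out: 25 / (1 − 0.20) = 31.25, rounded up to 32.
- Total: 3 × 32 = 96.

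All three figures reproduce. An exact t-test would need 26 (power 0.791 at 25), which is not material. The point therefore rests on how the analysis sets are worded, not on a wrong number.

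**2. The treatment-received condition, arm by arm.**

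| Meaning of the intervention | Moxibustion | Sham | Usual care |
|---|---|---|---|
| Real or sham sessions only | never-starters removed | never-starters removed | nobody qualifies (0 of 32) |
| The assigned arm's content, with usual care counting as an intervention | never-starters removed | never-starters removed | almost nobody removed |
| The brochure alone, for everyone | almost nobody removed | almost nobody removed | almost nobody removed |

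The second row is the sensible reading. The end of the Background names usual care among the interventions compared, the Intervention section covers all three arms, and the paragraph on secondary outcomes speaks of interventions in three groups. On that reading moxibustion and sham share one rule, and usual care is in effect exempt from it. The third row would make the condition empty.

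**3. The assessment condition.** It asks for data after random allocation, not after baseline. The Study schedule section describes allocation first and then baseline measures before the first intervention. A baseline score taken after allocation might therefore satisfy it, in which case this condition removes few people. The text does not settle this.

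**4. Size of a possible shift (illustration only).** The document does not say how many would be removed or how they would have fared. If a fraction of an arm is removed and their mean BFI change differs by g points from those kept, then

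mean of those kept − mean of all randomised = fraction × g.

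With the same g in both arms, the between-group difference shifts by about f × g, where f is the extra fraction removed from moxibustion compared with usual care. Equal removal with equal gaps gives f = 0 and no shift.

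| f (assumed) | Participants in an arm of 32 | g (assumed) | Shift, BFI points | Share of 1.6 |
|---|---|---|---|---|
| 0.05 | 1.6 | 1.6 | 0.08 | 5% |
| 0.10 | 3.2 | 1.0 | 0.10 | 6% |
| 0.10 | 3.2 | 1.6 | 0.16 | 10% |

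The shift favours moxibustion if those removed would have improved less than those kept. The yardstick of 1.6 was planned for moxibustion versus sham; the article gives no planned difference for H01.

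**5. Effect of an all-randomised primary set on sample size.** None: 32 per group and 96 in total stand. By normal approximation, power for moxibustion versus sham is 0.807 with 25 per group analysed and 0.893 with 32. The second figure is an upper bound that assumes complete data; with imputed outcomes it would be lower.

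**The case against.** The case for leaving the plan alone has real force.

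- **The convention is familiar.** Many trials use a full analysis set that omits people who were never treated and people with no data after randomisation. That stands as a description of practice. It is harder to defend where one arm has no treatment to start, its participants know their allocation and the outcome is self-reported.
- **The number affected may be small.** This also stands. Participants who drop out after starting stay in the FAS and are covered by imputation. Only those who fail entry are lost, and the baseline timing may mean that the assessment condition removes few.
- **The article does not forbid an ITT efficacy analysis.** True, and an analysis plan that is not shown might add one. The article nevertheless fixes which set is primary and which comparison is the sensitivity analysis, and the all-randomised set is in neither.

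Three stronger readings are tempting and are not supported.

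- A reader might infer that the rule deletes the whole usual care arm, so that H01 cannot be tested. The document's own use of the word intervention covers usual care, and H01 presupposes that the arm is analysed. The defect is an undefined and unequal condition, not an impossible one.
- A reader might infer that H02 is also filtered by different rules. Moxibustion and sham have the same entry rule and the same session schedule, and participants in both are to be blinded.
- A reader might infer that the exclusion criterion on fatigue therapies started during the trial removes randomised participants in the same way. The FAS definition carries no eligibility condition, and the section on concomitant treatment already says that new treatments are recorded.

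**Conclusion.** The concern holds in a limited form. The primary efficacy set depends on treatment received, that condition is undefined for usual care, and on the sensible reading it removes never-starters from moxibustion and sham but almost nobody from usual care. The inequality lies in H01, and it reaches H02 only because H01 is the gate. No efficacy analysis of everyone randomised is stated, and the one stated sensitivity comparison cannot expose the problem.

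The size is unknown. Shifts of 0.08 to 0.16 BFI points follow from assumed excess removals of 5% to 10% in the moxibustion arm and an assumed gap of 1.6 points. They would be zero if losses and gaps matched across the two arms. This is a modest risk, not proof of bias, but it falls on the comparison that controls the confirmatory sequence and is cheap to remove.

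**What to change.** Make the ITT set (all randomised, analysed as randomised) the primary set for efficacy, and apply the multiple imputation already planned to missing week-9 BFI scores. Keep the FAS and PP sets as sensitivity analyses.

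If the FAS is retained, delete the treatment-received condition from its definition, and state whether a baseline assessment made after allocation satisfies the assessment condition.

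The cost is rewording. Both the all-randomised set and the imputation method are already in the plan, the sample size does not change, and the Trial status section says that recruitment is still under way. The downside is that the estimate may be slightly less favourable and will depend on imputation for participants with little data. Eligibility requires a BFI score of at least 4, so every properly enrolled participant should have at least a screening score to inform the imputation.

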### Study schedule of enrolment, allocation, and assessments

After eligibility screening of the candidate participants who had signed informed consent, the participants will be randomly allocated to one of the three groups. Before the initial intervention begins, baseline measures will be obtained. After four weeks of intervention, outcomes reflecting the level of fatigue will be assessed at week 5. Post-treatment assessments will be conducted at week 9 after completing eight weeks of intervention. The follow-up visit will be planned at week 13, concluding the trial. The schedule of the enrolment, interventions, and assessments is given in Table 1.

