#### Safety outcomes

The participants will be instructed to voluntarily report all AEs that occurred during the trial. The investigators will determine whether the participants experienced any AEs via inquiries at each visit and checking for changes in laboratory tests from baseline to week 9. The laboratory tests will include complete blood count, differential count, absolute neutrophil count, aspartate aminotransferase, alanine aminotransferase, total bilirubin, gamma-glutamyl transferase, blood urea nitrogen, creatinine, albumin, glucose, hemoglobin A1c, erythrocyte sedimentation rate, CRP, thyroid-stimulating hormone, free thyroxine, and human chorionic gonadotropin urine test (only for women in their childbearing years at screening visit). All AEs identified during the trial will be recorded in the clinical record form.

The severity of AEs will be classified into five grades according to the common terminology criteria for AEs (CTCAE, version 4.0) developed by the National Cancer Institute as follows: mild, moderate, severe, life-threatening, or death [38]. In cases for which the CTCAE is not applicable, Spilker’s three level criteria will be used, and the AE will be classified into one of the three levels: mild, moderate, and severe [39].

A causal relationship between an AE and the moxibustion treatment provided in this study will be evaluated based on factors such as the temporal relationship, combined therapy, and underlying diseases, etc. The result of the causal relationship assessment will be categorized to one of the following six criteria: definitely related, probably related, possibly related, probably not related, definitely not related, or unknown.

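### The safety analysis uses no set defined by exposure: the primary ITT set can modestly dilute adverse event rates, and the per-protocol supplement drops participants who leave because of harm

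*Protocol article*

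**What the plan says.** The Statistical analysis section announces the sets with "Three types of analysis sets will be used in this study" and defines them as follows.

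- ITT: "The ITT analysis set will be comprised of the data from every participant who had been randomly assigned to any group in this trial". There is no condition on exposure.
- FAS: "all participants who ever received the intervention and provided assessment data at least once following random allocation". This set is assigned to efficacy.
- PP: "The PP set will include only the data from participants who completed the trial without any major violation of the protocol".

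The safety rule is "For safety analysis, the ITT set will be the primary set, and the PP set will be used as a supplement". No set is defined by exposure alone, and none groups participants by the treatment they actually received.

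Under Safety outcomes, AEs are found through voluntary reports and "via inquiries at each visit and checking for changes in laboratory tests from baseline to week 9", and every AE identified is to be recorded. The study schedule section puts random allocation first and then says "Before the initial intervention begins, baseline measures will be obtained". A participant can therefore be randomised and leave before any session.

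**The concern.** A safety table should show how often harm occurred among people exposed to the treatment. Neither set named for safety is built for that.

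The ITT set has the wrong denominator for this purpose if anyone randomised to a device arm never has a session. It also credits any harm to the assigned arm.

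The PP set has a more serious fault, because membership depends on completing the trial and harm is one reason for not completing it. The loss may also differ between arms. The electrical device in the moxibustion arm reaches a plateau of 45 °C at its base, while the sham devices are insulated or controlled to block heat transfer. Heat-related withdrawals would probably fall mostly in the moxibustion arm, so a PP table could lower that arm's rate selectively.

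Safety is a stated aim beside efficacy, and the Background faults earlier moxibustion trials because most did not report AEs and drop-outs. The safety tables should therefore be sound.

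**Working it through.** **Arm size (the plan's own figures).** Inputs from Sample size calculation: difference 1.6, SD 2.0, two-sided 5% level, 80% power, 20% drop-out.

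- n per group = 2 × (1.96 + 0.84)² × 2.0² / 1.6² = 24.5, rounded up to 25. This reproduces the stated 25.
- 25 / (1 − 0.20) = 31.25, rounded up to 32 per group; 3 × 32 = 96. Both agree with the article.

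I therefore use 32 randomised per arm and about 25 completers (32 × 0.80 = 25.6). The article gives no expected number of AEs, non-starters or AE-related withdrawals. The counts below are assumptions, shown over a range.

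**ITT denominator.** Assume 6 treated participants in one arm have an AE and u of the 32 never start. The ITT rate is 6/32; the rate among the treated is 6/(32 − u).

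| Never started (u) | ITT | Among treated |
|---|---|---|
| 0 | 6/32 = 18.8% | 6/32 = 18.8% |
| 1 | 6/32 = 18.8% | 6/31 = 19.4% |
| 3 | 6/32 = 18.8% | 6/29 = 20.7% |
| 6 | 6/32 = 18.8% | 6/26 = 23.1% |

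The dilution is nil with no non-starters and 20.7 − 18.8 = 1.9 percentage points with 3.

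**PP supplement.** Take the same 6 AE patients and 25 completers, and let h of the 6 leave the trial because of the AE. The PP rate is (6 − h)/25. The comparator is 6/32 = 18.8%, the rate when all 32 were treated.

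| Left because of AE (h) | PP |
|---|---|
| 0 | 6/25 = 24.0% |
| 1 | 5/25 = 20.0% |
| 2 | 4/25 = 16.0% |
| 3 | 3/25 = 12.0% |

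The same six events give anything from 24% to 12%, depending only on who left. If few AE patients leave, PP lies above 18.8% because unaffected drop-outs shrink the denominator. From h = 2 it lies below. PP can therefore mislead in either direction, and it understates harm in the case that matters most for safety.

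**Is the FAS a ready substitute?** No. It requires exposure but also a later assessment, so a treated participant who left early with a reaction could fall outside it.

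**The case against.** The strongest reply is that the primary safety analysis is sound on the main issue. A participant who stops after a reaction stays in the ITT set, and the event is recorded. A reader might infer from the safety rule that the plan as a whole removes people harmed by treatment. The documents do not support that; only the supplementary table can lose them. This part of the reply stands in full and limits the severity.

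The dilution is also hypothetical. It disappears if everyone starts, and it is under 2 percentage points with 3 assumed non-starters. That stands too. Grouping by treatment received is likewise a matter of sound definition: the article gives no sign that device mix-ups are expected, and the unblinded practitioners open the envelopes themselves.

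The PP exclusion depends on leaving the trial or on what counts as a major violation, which the article does not define. Someone who stops sessions but attends to week 13 might remain in PP. That narrows the point to participants who leave the trial or are classed as major violators, and does not remove it.

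A reader might also infer that any AE contrast with usual care is biased, because "The investigators will determine whether the participants experienced any AEs via inquiries at each visit" and the device arms attend treatment sessions that usual care does not. The documents do not carry this. The schedule table is not shown, so usual-care visits cannot be counted. Voluntary reports and laboratory checks are not tied to sessions, and the article singles out no AE comparison with usual care.

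**Conclusion.** The point holds with limited size. The article states the safety rule outright, so this is not a detail left to another document. By the article's own definitions, ITT counts never-treated participants under their assigned arm, and PP omits anyone who leaves the trial because of harm.

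The ITT effect is small and conditional on there being non-starters. The PP effect can be larger: under the assumed counts, three AE-related departures among six AE patients halve the PP rate from 24% to 12%. The expectation that this falls mainly on the heated arm is a judgement from the device descriptions and has not been shown in data.

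Severity is minor to moderate. Every harmed participant stays in the primary analysis, and the sample size, significance level, primary outcome and AE collection are unaffected.

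**What to change.** In the Statistical analysis section, replace the safety rule with one safety set: all participants in the moxibustion and sham arms who had at least one device application, grouped by the treatment actually received, plus all participants randomised to usual care. Require no later assessment for entry, so that early withdrawals stay in. Delete the PP safety analysis.

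Do not restrict the usual-care comparison to AEs elicited at weeks 5, 9 and 13. That could discard reactions reported at treatment sessions and so understate harm in the device arms.

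The cost is wording and table shells. AE rates may look slightly less favourable than under the present rule.

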**Methods/design:**

A multi-center, three-armed parallel, randomized controlled trial will be conducted. Ninety-six patients with cancer-related fatigue will be recruited from three clinical research centers. They will be randomly allocated to one of three groups in a 1:1:1 ratio. The moxibustion group will receive moxibustion treatment at CV8, CV12, LI4 and ST36. The sham moxibustion group will receive sham moxibustion at non-acupoints. Both the moxibustion and sham moxibustion groups will receive 30-min treatments twice a week for 8 weeks. The usual care group will not receive moxibustion treatment. All participants will be educated via a brochure on how to manage cancer-related fatigue in daily life. The outcome measurements will be evaluated at baseline, week 5, week 9, and week 13 by assessors who are blinded to the group allocation. The primary outcome measure will be the mean change in the average scores of the Brief Fatigue Inventory before and after treatments between groups. The secondary outcome measures will be the mean difference in changes from baseline of the Brief Fatigue Inventory, functional assessments of cancer therapy-fatigue, European Organization for Research and Treatment of Cancer Quality of Life Questionnaire C-30 scores, and Montreal Cognitive Assessment scores between groups. Safety will be assessed by monitoring adverse events at each visit.

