## Discussion

The purpose of this study is to assess the efficacy and safety of moxibustion treatment for patients with cancer-related fatigue.

Cancer-related fatigue is one of the most prominent manifestations of cancer survivors that can be occur over a long period of time even after the end of cancer treatment or the complete remission of cancer [3]. Although the prevalence of cancer-related fatigue varies among studies, it is generally reported that approximately 60 to 100% of cancer survivors experience cancer-related fatigue [43]. Cancer-related fatigue lowers the QOL of the family of the patient in addition to the cancer patient and can become a socially obvious burden [5–7]. Although a variety of pharmacologic and nonpharmacologic therapies for treating cancer-related fatigue have been evaluated in the clinical trials, no treatments have been confirmed as valid and safe for long-term use [17, 19]. Therefore, it is important to confirm whether moxibustion, one of the oldest but most popular therapies in traditional East Asian medicine, including Korean medicine, is a viable therapeutic option for the management of cancer-related fatigue.

The moxibustion treatment regimen was established based on the findings of the relative studies that were previously published. Although there were few studies with good quality evaluating the effect of moxibustion for the patients with cancer-related fatigue, a recent publication by Mao et al. [32]. using infrared laser moxibustion was helpful. Mao et al. [32]. reported that the moxibustion reduced the BFI score during the 4-week treatment period, however, it tended to stagnate at follow-up session at week 8. Another study by Mao et al. [44] targeting the breast cancer patients with psychological distress including cancer-related fatigue was also reliable even though its intervention was electroacupuncture, not moxibustion. According to this study, the BFI score decreased during the 8-week of treatment period, and then the improvement trend was stopped 4 weeks after the completion of the treatment. Therefore, we expect to see how the BFI will change during and after the 8-week treatment period.

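### The per-protocol set should not supplement the safety analysis, because it drops participants who leave the trial over an adverse event; a set of treated participants is needed instead

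*Protocol article*

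**What the plan says.** All the relevant text is in the Statistical analysis section of the protocol article, which names three analysis sets and no separate safety set.

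- Intention to treat (ITT): "The ITT analysis set will be comprised of the data from every participant who had been randomly assigned to any group in this trial". There is no condition on having been treated.
- Full analysis set (FAS): "The FAS set will include the data from all participants who ever received the intervention and provided assessment data at least once following random allocation". This is the only set that requires receipt of the intervention, and it is assigned to efficacy.
- Per-protocol (PP): "The PP set will include only the data from participants who completed the trial without any major violation of the protocol".

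Safety is then assigned explicitly: "For safety analysis, the ITT set will be the primary set, and the PP set will be used as a supplement".

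Safety is one of the trial's aims. The Discussion opens with: "The purpose of this study is to assess the efficacy and safety of moxibustion treatment for patients with cancer-related fatigue". The Safety outcomes section has adverse events asked about at every visit and every identified event recorded.

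**The concern.** A supplementary safety analysis should show whether the main safety result holds in another reasonable population. The PP set cannot do that, because membership depends on completing the trial, and an adverse event can be the reason a participant does not complete. The events lost this way are those serious or unpleasant enough to make someone leave, and they are the most informative about tolerability. A low PP event rate would then partly reflect how the set was built.

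A second, smaller point concerns the primary set. It is defined by randomisation alone, so a participant allocated to moxibustion or sham who never attends a session stays in that arm's denominator as if exposed. Neither set used for safety is defined by treatment received.

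What is at stake is a misleading secondary safety table in a trial that names safety as an aim. The primary safety count is not at stake.

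**Working it through.** **1. Base figures from the plan.** The Sample size calculation section gives a difference of 1.6, SD 2.0, two-sided 5% significance, 80% power and 20% drop-out.

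- n per group = 2 × (1.96 + 0.84)² × 2.0² / 1.6² ≈ 24.5, rounded up to 25.
- Allowing for drop-out: 25 / 0.8 = 31.25, rounded up to 32. Three groups give 96.

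The plan's figures are reproduced. They are not in dispute and serve only as the base for the illustration.

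**2. Size of the PP set.** 20% of 32 is 6.4, so take d = 6 drop-outs per arm. With no further exclusions for major violations, PP has 32 − 6 = 26 participants.

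**3. Formulas.** Let *a* be the participants in an arm with an adverse event, and *w* those among them who leave the trial because of it. Suppose the remaining drop-outs had no event.

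- ITT rate = a / 32
- PP rate = (a − w) / 26

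PP is below ITT exactly when w/6 is greater than a/32, that is, when events are more common among drop-outs than in the arm as a whole.

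**4. Results.** The values of *a* and *w* are assumptions; the protocol gives no adverse event rates and does not say why participants would drop out.

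| Participants with an event (a) | Withdrew because of it (w) | ITT | PP |
|---|---|---|---|
| 4 | 2 | 4/32 = 12.5% | 2/26 = 7.7% |
| 6 | 3 | 6/32 = 18.8% | 3/26 = 11.5% |
| 6 | 6 | 6/32 = 18.8% | 0/26 = 0% |
| 3 | 0 | 3/32 = 9.4% | 3/26 = 11.5% |

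The third row is the extreme case: PP reaches zero only when no completer has an event. The last row shows the opposite direction: when all events occur in completers and drop-out is unrelated to harm, PP is the higher of the two.

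**5. Dilution in the primary set.** Let *u* be the device-arm participants randomised but never treated (also assumed).

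- 3 events, u = 2: 3/32 = 9.4% against 3/30 = 10.0% among the treated.
- 6 events, u = 1 to 3: 6/32 = 18.8% against 6/31 = 19.4% to 6/29 = 20.7%.

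The largest gap here is about 2 percentage points, against about 7 for PP in the second row of the table.

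**The case against.** The strongest reply is that the primary safety analysis loses nothing. It includes every randomised participant, and all identified events are recorded, so an event that precedes withdrawal counts in the main result. Only a supplement is affected, and the article attaches no decision or claim to agreement between the two sets. This stands, and it limits the weight of the point.

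A second reply is that stopping treatment is not the same as leaving the trial. The study schedule ends with a follow-up visit at week 13. Someone who stops sessions after an adverse event but attends follow-up could stay in PP, unless stopping counts as a major violation. The article does not define that term, and such detail is commonly left to fuller documents. This also stands: the loss is certain only for participants who leave the trial.

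Three stronger readings are tempting, and the document does not support them.

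- A reader might infer that both safety sets push the device-arm event rate down. For PP this depends on who drops out, as the last row of the table shows; for ITT the effect is small.
- A reader might infer from the matching appearance of the real and sham devices that participants will be counted under a device they did not receive. Only the front views match: the bases differ, the body sites differ, and the practitioners are unblinded and open the allocation envelopes themselves. No rate of mix-up is given or implied.
- A reader might infer from the general sentence on multiple imputation that adverse events will be imputed. It does not say so, and an explicit exception for safety data belongs in an analysis plan.

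**Conclusion.** The point holds as a defect in the supplementary safety analysis, with a minor inefficiency in the primary one. The article states the choice of PP outright, so it is not a detail awaiting an analysis plan. Because PP is conditioned on completion, which harm can prevent, its event rate cannot corroborate the primary result.

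With 32 per arm, 6 drop-outs and half of 6 event-affected participants withdrawing because of the event, PP would show 11.5% where the full arm shows 18.8%. That size rests on assumed event counts. A PP rate of 0% requires every event to end in withdrawal, and it would be wrong to present that as the expected result. It would also be wrong to conclude that the trial's main safety result is biased by lost events. The weakness of the primary set is only that it counts untreated device-arm participants as exposed, which moves the rate by roughly 0.6 to 2 percentage points in the cases examined.

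**What to change.** Replace the safety sentence in the Statistical analysis section with a defined safety set, for example: safety will be analysed in all participants of the two device arms who received at least one session, grouped by the intervention actually received, together with all participants of the usual care group; the PP set will not be used for safety.

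The FAS is not a ready substitute. It adds a requirement for assessment data, which could leave out a treated participant who withdraws early, and it does not say that participants are grouped by intervention received.

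The change takes a sentence or two. It needs no new data and does not alter the sample size or the efficacy analysis. The one downside for the sponsor is that the device-arm event rate may look slightly less favourable once never-treated participants leave the denominator.
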